##### **Statistics:**

A sample size of 800 patients/stent type (753 plus compensation for a withdrawal rate of 5 to 6%) would provide a power of more than 90% to detect, at an alpha level of 0.05 in a two

tailed test, a significant difference between the BMS group and the DES group. This sample size will also allow to detect a significant difference between the BMS and each of the DES groups with a power of 80% at an alpha level of 0.027.

Intention to treat analysis: bivariable group comparisons will be first performed, then time to event will be evaluated both by Kaplan Meier statistics and Cox-regression analysis taking into account influential factors.

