## **10. Data handling and Analyses**

Data management will be based on experience in other large multicenter trials (17,30). Thus, an internet-based electronic CRF will be used for data management. A secure website, accessible by password only, will be provided for data entry. Data will be stored centrally using an SQL-database. Quality of data will be assured by regular on-site monitoring visits, comparing data entered in CRFs with source documents. After monitoring, changes in CRF will be done electronically and only be possible by monitors and study coordination.

The following data will be recorded, in analogy to BASKET-PROVE I:

- Patient history and demographics
- CAD risk factors
- Comorbidities
- Indication for PCI
- Baseline angiographic and procedural characteristics
- Relevant data of stent use and concomitant drug use
- Serious adverse events during follow-up

- Events during follow-up (i.e. all hospitalisations, all coronary interventions, all bleeding, death)
- EQ-5D

For the statistical analysis, the data will be extracted from this database and transferred to and analysed in the commercially available statistical package SPSS v.15.0.

Bivariable comparisons of the DES group with the BMS group will be done using Fisher's exact test for proportions and the Mann-Whitney U-test, for continuous variables. P-values for the comparisons of each of the DES groups to the BMS group will be adjusted using the Bonferroni-Holm method if multiple comparisons of proportions or the Dunnett-Hsu if multiple comparisons of survival curves are performed. Time to event will be evaluated both by Kaplan Meier statistics and multivariable Cox-regression analysis taking into account further influential variables.

Historical comparisons of net clinical benefits will be only of descriptive character.

A priori, missing values will not be imputed. Losses to follow-up will be incorporated since survival analysis will be performed. If outliers values are observed, each will be examined. If it is thought that their cause is of clinical nature, they would be kept in the analysis, otherwise they will be set to missing.

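### The no-imputation and outlier rules make the adjusted Cox model complete-case by default, although the synopsis lists it under intention to treat

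*Protocol*

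**What the plan says.** Section 10 (Data handling and Analyses) sets three rules on incomplete or doubtful data.

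- Missing data: "A priori, missing values will not be imputed".
- Withdrawals: "Losses to follow-up will be incorporated since survival analysis will be performed".
- Outliers: each is examined, and then "If it is thought that their cause is of clinical nature, they would be kept in the analysis, otherwise they will be set to missing".

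The same section plans a "multivariable Cox-regression analysis taking into account further influential variables". The covariates are not named.

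The synopsis (Statistics) puts every analysis under one label: "Intention to treat analysis: bivariable group comparisons will be first performed, then time to event will be evaluated both by Kaplan Meier statistics", and then "Cox-regression analysis taking into account influential factors".

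Three other statements bear on the point. Section 10 provides for source verification: "Quality of data will be assured by regular on-site monitoring visits, comparing data entered in CRFs with source documents", with electronic CRF changes allowed afterwards. Section 9 assigns Fisher's exact test to the BMS versus DES hypothesis and to the comparisons of BMS with each DES. Section 4 describes the trial as open-label; the only blinding to stent type is that of the endpoint committee, in section 8.

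**The concern.** A Cox model cannot use a patient who lacks a value for one of its covariates. If imputation is ruled out and nothing is put in its place, the model is fitted to complete cases. A randomised patient with one blank covariate then leaves the adjusted analysis, together with the follow-up and any death or MI. The sentence on losses to follow-up does not prevent this, because censoring deals with unobserved outcomes and not with unobserved covariates.

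The outlier rule adds to the blanks and is loosely drawn. It has two outcomes, keep or delete, and the analysis-stage rule has no option to correct the value. The test is an opinion about the cause of the value, not whether the source confirms it. Nothing requires that whoever decides be unaware of the stent type.

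What is at stake is the patient set behind the adjusted hazard ratio. Section 4 stresses that the trial depends on including emergency patients. It is a reasonable inference, though not stated, that their baseline data will be less complete. Section 6 gives both stent types 12 months of prasugrel in ACS, but in elective cases 1 month after BMS and 12 after DES. Selective loss of emergency patients would therefore shift the mix of patients over which the adjusted hazard ratio is averaged, even if the losses were equal between arms.

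**Working it through.** **1. The plan's own figure.** Section 9 gives 753 BMS and 1506 DES patients, event rates of 6.0% and 10.5% at 24 months, two-sided alpha 0.05 and power above 90%.

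- Expected events: 753 × 0.06 + 1506 × 0.105 = 45.18 + 158.13 = 203.3. Pooled rate: 203.3 / 2259 = 0.090.
- Standard error under the null: √[0.09 × 0.91 × (1/753 + 1/1506)] = 0.01277.
- Standard error under the alternative: √[0.06 × 0.94/753 + 0.105 × 0.895/1506] = 0.01172.
- z = (0.045 − 1.96 × 0.01277) / 0.01172 = 1.70, so power is 95.6%. Simulating Fisher's exact test also gives 95.6%.

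The stated power is reproduced.

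**2. Which analyses a blank covariate can reach.**

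| Analysis | Uses covariates? | Loses a patient to a blank covariate? |
|---|---|---|
| Fisher's exact test (section 9) | No | No |
| Kaplan-Meier (section 10, synopsis) | No | No |
| Multivariable Cox (section 10, synopsis) | Yes | Yes, unless a method is specified |

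Only the adjusted analysis is exposed.

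**3. Possible size of the loss.** The protocol gives neither the number of covariates k nor the share m of patients missing each one. Both are assumed here: k from 5 to 10, m from 0.1% to 3%, independent across covariates. The share lost is 1 − (1 − m)^k. Patients lost are that share of 2259. Events lost are that share of 203, which supposes that those lost have average risk.

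| k | m | Share lost | Patients | Events |
|---|---|---|---|---|
| 5 | 0.1% | 0.5% | 11 | 1 |
| 10 | 0.5% | 4.9% | 110 | 10 |
| 5 | 1% | 4.9% | 111 | 10 |
| 10 | 1% | 9.6% | 216 | 19 |
| 10 | 2% | 18.3% | 413 | 37 |
| 10 | 3% | 26.3% | 593 | 53 |

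Independence pushes these shares up. If the blanks cluster in the same patients, the share lost falls towards m itself, that is, towards 0.1% to 3%. If the patients lost have above-average risk, the events lost exceed the proportional figures.

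**The case against.** The other side has several good points.

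- **The hypotheses do not rest on the Cox model.** A reader might infer that the primary comparison loses patients or falls below its stated power. It does not: section 9 tests the hypotheses by Fisher's exact test, which needs no covariates. The claim of more than 90% power belongs to that comparison, and the protocol claims no power for the Cox model. This stands in full.
- **Deletion is not written down.** It follows from how the model works when no other rule is given. The no-imputation sentence is also qualified as a priori, so it should not be read as a ban for all time. This stands as to wording, but the qualifier names no alternative.
- **The outlier rule is the smaller cause.** It bears mainly on continuous variables, and a blanked value matters only if that variable enters the model. The no-imputation rule drives the loss, whatever made the value missing. This stands.
- **Source monitoring already catches plain entry errors.** A weight entered as 700 kg where the source says 70 kg would probably be corrected before data extraction. This largely stands. What it leaves open is the value still doubtful at analysis, where opinion decides and return to source is not mentioned.
- **Bias between arms is not shown.** Emergency presentation precedes randomisation, so blanks due to it should fall evenly on the arms, and primary events are adjudicated blind to stent type. This stands for such blanks. It does not cover outlier decisions made with the stent type visible.
- **Such detail belongs in a statistical analysis plan.** One may exist and is not shown. The point here, however, is two rules that the protocol does state; a plan that kept all patients in the model would have to depart from them.

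**Conclusion.** The point holds for the adjusted analysis only. As written, section 10 yields a complete-case Cox model, while the synopsis lists that model under intention to treat. The outlier rule can add blanks by a judgement that has no criterion and no blinding. The loss could be trivial or considerable: about 0.5% to 26% of patients under the assumed 5 to 10 covariates and 0.1% to 3% independent missingness, and less if the blanks cluster. None of these rates comes from the protocol.

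The documents do not support the stronger readings that the primary test is compromised, that the sample size is too small for this reason, or that the BMS versus DES comparison is shown to be biased. This is an inexpensive improvement to a supporting analysis and worth making, because the present wording and the intention-to-treat label do not fit together.

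**What to change.** Replace the two sentences in section 10.

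1. **Outliers.** Check each outlier against source before the analysis, by someone blinded to stent type. Correct it to the source value if the two differ, keep it if the source confirms it, and set it to missing only if it is implausible and cannot be verified.
2. **Missing data.** Do not impute outcomes. Fill missing baseline covariates in the Cox model by a prespecified method that ignores stent type, for example the overall mean or mode, so that every randomised patient stays in the adjusted analysis. Report the complete-case result as a sensitivity analysis.

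The cost is slightly more programming and reliance on a simple imputation assumption, which the sensitivity analysis lets the reader judge. No extra patients, visits or data are needed, and the tests of the hypotheses and the sample size stay as they are.

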## **11. Finances/Insurance**

The stents will be used as clinically indicated and therefore paid by the health insurance. In fact, the rate of the more expensive DES will only be 2/3 in this study,

compared to the average of 85% overall in Switzerland 2007, resulting in reduced overall health care costs.

Follow-up questionnaires and event documentation as well as analyses will be paid by a special study grant.

The study will be planned, conducted, analysed and interpreted entirely independently from industry and will be entirely founded by research grants of the Basel Cardiovascular Research Foundation and the University of Basel. The concomitant medication is provided for free to all patients by the European Alliance of Ely Lilly Europe.

Since no “investigational” devices will be used (all stents are CE marked and freely available on the market in Switzerland and Denmark) this is in fact an observational clinical study only. A special insurance for all included patients in Switzerland, Austria and Germany will be effected with the Zürich insurance-company before enrolment of the first patient.

## **12. Ethics**

The study protocol undergoes approval by the Ethics Committee of each centre. Each patient will be asked to give written informed consent to participate in this study and its follow-up (see above). The study will be conducted according to the GCP-Guidelines.

## **13. Time plan**

Approval of the protocol: Summer 2009

|                                |                                                                                             |
|--------------------------------|---------------------------------------------------------------------------------------------|
| Ethical approval:              | Autumn 2009                                                                                 |
| Start of study:                | January 2010 (Basel; other centres as soon as ethical approval is available at each centre) |
| Inclusion completed:           | Spring 2011                                                                                 |
| Last follow-up completed:      | Spring 2013 (24months)
Spring 2015 (60 months)                                           |
| First presentation of results: | ESC 2013                                                                                    |

## **15. Clinical Relevance**

If findings of the retrospective analysis of BASKET/BASKET-LATE (12) are verified by the prospective BASKET-PROVE and BASKET-PROVE II trials, then the 1st generation DES may no longer be used for large native vessel stenting. This would reduce the late harm related to late stent thrombosis which includes late cardiac death, which is most relevant in view of the >6 million DES implanted per year worldwide today. In addition, it would reduce costs considerably due to the much lower price of BMS vs. DES. If, however, findings do not confirm results of BASKET-LATE then the “late harm” observed there was a “chance” finding and not relevant further, or to a much lesser degree than postulated in BASKET-LATE. If findings differ between different stent types, results will help define the most safe and effective stent type to treat patients in need for large vessel stenting. In addition, results of the study will help to understand mechanisms of late stent thrombosis: if

late clinical events related to late stent thrombosis do no longer or to a lesser extent occur with newest generation DES with a bioabsorbable polymer, then late stent thrombosis is most likely due to the polymer and not to the drug or drug-dose used. By the historical comparison of the XienceV® stent-arms of BASKET-PROVEII with BASKET-PROVE, the analysis will provide also the unique chance to test the performance of the most widely used DES with dual antiplatelet therapy based on Prasugrel versus Clopidogrel in an unselected real-world population. – Thus, these findings should have major impact on the current use of coronary stents and our understanding of possible reasons for late stent thrombosis.

## **Appendix 1**

**SEPT 14, 2006**

### **FDA Statement on Coronary Drug-Eluting Stents**

FDA is providing the following information in response to inquiries asking for the agency's position on adverse events related to coronary drug-eluting stents (DES). This information describes our position at this time and does not represent new agency policy.

FDA has been closely monitoring DES since they came to the United States market in 2003 and 2004 - and will continue to do so.

We are aware of recent data suggesting a small but significant increase in the rate of death and myocardial infarction (heart attack) possibly due to stent thrombosis (a blood clot in the stent) in patients treated with DES. The specific studies that have prompted recent media inquiries are the BASKET-LATE study (presented at the March 2006 American College of Cardiology Scientific Sessions in Atlanta, Ga.) and more recently, the Camenzind meta-analysis (presented at the September 2006 European Society of Cardiology Annual Meeting/World Congress of Cardiology Meeting in Barcelona, Spain). The small but significant increase in the rate of death and myocardial infarction observed in these studies was noted in patients followed 18 months to 3 years after stent implantation.

While the studies presented at the Atlanta and Barcelona meetings have raised important questions, the data we currently have do not allow us to fully characterize the mechanism, risks, and incidence of DES thrombosis. A more formal evaluation of the data in these studies is necessary, and any conclusions are dependent upon a thorough peer review. FDA intends to more formally evaluate the studies presented in Atlanta and Barcelona.

Stent thrombosis in patients who receive DES is a primary area of interest for the agency because of the potential for serious adverse outcomes-even though stent thrombosis occurs at low rates. Over the past two months, the agency has met with both manufacturers of the FDA-approved approved DES to discuss any information and perspectives they have that may be pertinent to this issue. In assessing the risk of stent thrombosis, we remain keenly interested in the long-term follow-up of patients enrolled in the original pivotal DES randomized trials as well as those in the more complex patient and lesion subsets (for example, patients with diabetes; acute myocardial infarction or multiple vessel disease; or lesions involving arterial bifurcations, the left main coronary artery, and long arterial segments) who are currently being treated in "real world" randomized and registry studies.

FDA also continues to closely evaluate information related to the duration of treatment with clopidogrel (Plavix), a drug used in combination with aspirin to reduce/prevent clotting in DES patients. Although the duration of clopidogrel appeared to be adequate for the selected patients in the original clinical trials conducted to support FDA approval, the agency recognizes that the optimal duration of clopidogrel in more complex patients has not been defined. The recommended duration of clopidogrel administration and patient compliance with the prescribed regimen are likely interrelated with patient and anatomical factors that are associated with DES thrombosis. Additional clinical data are likely needed to reach conclusions regarding the optimal antiplatelet therapy regimen for DES patients.

FDA will convene a public meeting of the Circulatory System Devices Advisory Panel by the end of the year in an effort to improve our knowledge regarding the incidence and timing of stent thrombosis as well as the appropriate duration of clopidogrel use in patients who receive DES. This Panel of outside experts will assist the agency in the review and analysis of the available scientific data and provide recommendations for appropriate actions to address this issue, such as possible changes to device labeling or the need for additional clinical studies. An announcement of this meeting will appear on FDA's web site, [www.fda.gov/cdrh](http://www.fda.gov/cdrh) <<http://www.fda.gov/cdrh>>.

At this time, FDA believes that coronary DES remain safe and effective when used in patients having clinical and coronary anatomic features similar to those treated in the pivotal trials conducted by the manufacturers for FDA approval. The approved indications are:

- The CYPHER Sirolimus-eluting Coronary Stent is indicated for improving coronary luminal diameter in patients with symptomatic ischemic disease due to discrete *de novo* lesions of length  $\leq 30$  mm in native coronary arteries with reference vessel diameter of  $\geq 2.5$  mm to  $\leq 3.5$  mm.
- The TAXUS Express Paclitaxel-Eluting Coronary Stent System is indicated for improving luminal diameter for the treatment of de novo lesions  $\leq 28$  mm in length in native coronary arteries  $\geq 2.5$  to  $\leq 3.75$  mm in diameter.

For more information, see <<http://www.fda.gov/cdrh/pdf2/P020026.html>> and <<http://www.fda.gov/cdrh/pdf3/P030025.html>>.

For thousands of patients each year, these devices have resulted in a significant reduction in the need of second procedures to treat restenosis. The FDA will continue to carefully evaluate all DES data in an attempt to maximize the benefits and minimize the risks for patients undergoing this therapy for treatment of their coronary artery disease.

To summarize:

- FDA has been monitoring coronary drug-eluting stents closely since they came on the U.S. market in 2003 and 2004, and will continue to do so.
- New data were released recently that suggest a small but significant increased risk of stent thrombosis in patients who have drug-eluting stents. The agency is keenly interested in this issue because of the potential for serious harm to patients-even though stent thrombosis occurs at low rates.
- While the new data are of interest to FDA and raise important questions, we do not have enough information yet to draw conclusions. It's unclear, for example, what causes drug-eluting stent thrombosis, how often it occurs, under what circumstances it occurs, or what the risk of occurrence is in a given patient.
- To better understand this issue, FDA met with the two manufacturers of these products in recent months to discuss any information they might have pertaining to this issue and get their perspective. In addition, we plan to convene a public panel meeting of outside scientific experts in the near future to assist us in a thorough review of *all* the data and make recommendations about what actions may be appropriate, such as possible labeling changes or additional studies.

At this time, FDA believes that coronary drug-eluting stents remain safe and effective when used for the FDA-approved indications. These devices have significantly reduced the need for a second surgery to treat restenosis for thousands of patients each year.

## Appendix 2

### Pharmacovigilance

#### 1 Defining Adverse Events

An adverse event (AE) is any untoward medical occurrence in a patient during or following administration of an investigational product and which does not necessarily have a causal relationship with treatment. An AE can therefore be any unfavourable and unintended sign (including an abnormal laboratory finding), symptom, or disease temporarily associated with the use of the trial drugs, whether or not considered related to the trial drugs.

#### 2 Defining Serious Adverse Events (SAEs)

A Serious Adverse Event is defined in general as an untoward (unfavourable) event, associated with trial drug or trial procedure, which:

- is fatal. Death may occur as a result of the basic disease process. Nevertheless, all deaths occurring within 30 days of the last administration of the study agent must be treated as an SAE and reported as such. All deaths which may be considered as related to the trial agent, regardless of the interval, must be treated as a SAE and reported as such.
- is life-threatening
- requires or prolongs hospitalisation
- results in persistent or significant disability or incapacity
- is a congenital anomaly or a birth defect, or
- may require medical or surgical intervention to prevent one of the outcomes listed above
- Any other significant clinical event, not falling into any of the criteria above, but which in the opinion of the investigator requires reporting.

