# STUDY PROTOCOL

## 1. Background

BASKET was a prospective study to test the cost-effectiveness of drug-eluting stents (DES) versus bare-metal stents (BMS) in a „real-world“ setting, i.e. in all-comers for percutaneous coronary interventions (PCI) irrespective of indication (1). This trial showed that DES (Cypher®, Cordis, Johnson & Johnson, Miami Lakes, Florida, USA or TAXUS®, Boston Scientific Corporation, Natic, Massachusetts, USA, randomized 1:1) were not cost-effective compared to BMS (Vision®, Guidant Corporation, Indianapolis, Indiana, USA, DES:BMS = 2:1 randomization) at an incremental cost-effectiveness ratio to prevent one clinical event of € 18'031 after 6 months or € 53'094 after 18 months (2). In high risk subgroups such as small vessel stenting, multivessel disease, long lesions, multiple stenting and elderly patients, however, DES were more cost-effective or even cost-saving. BASKET-Late Thrombotic Events (BASKET-LATE), a follow-up investigation of clinical events up to 18 months (month 7 to 18) after discontinuation of clopidogrel identified an excess in late cardiac death/non-fatal myocardial infarction (MI) in patients treated with DES compared to those treated with BMS (3), which was true also after 36 months (4). There was a strong indication that these late clinical events were related to late stent thrombosis. These findings were indirectly confirmed by a large registry of patients from Berne and Rotterdam (5) showing a rate of late angiographically documented stent thrombosis of 0,6% per year during the first 3 years of follow-up in patients treated with DES, an effect not seen after BMS stenting.

Predictors of late clinical events in BASKET-LATE were use of glycoprotein IIb/IIIa inhibitors (as measure of acute coronary syndromes or suboptimal PCI results), prior MI and DES use, and in the Berne/Rotterdam registry the only independent predictor of late stent thrombosis was acute coronary syndrome. A more profound analysis of subgroups benefiting from DES was performed based on the overall BASKET/BASKET-LATE data after 18 months (6).

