#### 3 Defining Suspected Unexpected Serious Adverse Reactions (SUSARs)

All SAEs assigned by the local investigator as both suspected to be related to the trial drugs and unexpected are subject to expedited reporting. An event is unexpected when information is not consistent with the available product information or investigator brochure, or if they add significant information on the specificity or severity of an expected reaction

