## 5 Reporting SAEs

SAEs will be collected for all patients beginning with informed consent. Serious ADRs, which are SAEs considered to be drug-related (at least possibly related), must be reported to the MAH regardless of the time that has elapsed since the end of the trial.

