## 6 Reporting SUSARs

All SAEs assigned by the local investigator as both suspected to be related to study protocol (treatment/procedures) and unexpected (see definition in section 3) will be reviewed by the Principal Investigators (PIs).

Such SAEs will be classified as SUSARs and will be subject to expedited reporting to concerned ethic committees (EC) and regulatory authorities (RA) according to definitions and timelines specified in the local laws and regulations and according to any specific requests made by regulatory authorities.

As a general guideline the following requirements should be used:

- SUSARs must be reported to the EC / RA within 7 calendar days of the PI (or their research team) being informed of the event, if they result in Death or are deemed to be life-threatening.
- Any SUSARs not resulting in Death or deemed to be life-threatening must be reported to the EC / RA within 15 Calendar days of the PI (or their research team) being informed of the event.

In addition, the sponsor shall inform all participating investigators of findings that could adversely affect the safety of study subjects. The information can be aggregated in a line listing of SUSARs in periods as warranted by the nature of the clinical development project and the volume of SUSARs generated. This line listing should be accompanied by a concise summary of the evolving safety profile of the investigational medicinal product.

All SUSARs occurring whilst on trial (until 30 days after the last day of the last treatment) must be reported.

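### Appendix 2 gives SUSARs two different scopes and counts its 30-day limits from the last dose, so late stent-related events can escape expedited and automatic death reporting

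*Protocol*

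**What the plan says.** All the rules at issue are in Appendix 2 (Pharmacovigilance) of the protocol.

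- **Section 2, SAE definition.** "A Serious Adverse Event is defined in general as an untoward (unfavourable) event, associated with trial drug or trial procedure", followed by the usual seriousness criteria. Under the fatal criterion two sentences on deaths are added: "all deaths occurring within 30 days of the last administration of the study agent must be treated as an SAE and reported as such", and "All deaths which may be considered as related to the trial agent, regardless of the interval, must be treated as a SAE".
- **Section 3, SUSAR definition.** SAEs that the local investigator considers "suspected to be related to the trial drugs and unexpected are subject to expedited reporting".
- **Section 4, AE collection.** From the first dose to 30 days after the last dose of a protocol IMP.
- **Section 5, SAE collection.** Starts at informed consent; no end is stated. Serious drug-related reactions "must be reported to the MAH regardless of the time that has elapsed since the end of the trial".
- **Section 6, SUSAR reporting.** SAEs "suspected to be related to study protocol (treatment/procedures) and unexpected" are classified as SUSARs, with a pointer back to section 3. It closes with "All SUSARs occurring whilst on trial (until 30 days after the last day of the last treatment) must be reported".

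Elsewhere, section 6 of the main text (Concomitant Therapy) plans prasugrel for 12 months after DES, or after BMS in ACS, and for 1 month after elective BMS, with aspirin throughout. Section 5 (Follow-up) runs to 24, 36 and 60 months. Section 8 sets the primary endpoint at 24 months.

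**The concern.** The trial randomises stents, and its rationale is late harm from stent thrombosis, including late cardiac death. A safety-reporting appendix for such a trial has to say plainly whether an event attributed to the stent is reportable, and for how long. Appendix 2 answers the first question in two ways. It answers the second with limits that follow the drug course, and in elective patients that course differs by randomised arm.

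Two centres that each follow the text in good faith could send different events to ethics committees and authorities. A fatal stent occlusion at month 20, for example, falls outside the 30-day death rule if the agent is prasugrel. It falls under the open-ended death rule only if it is considered related to an agent that the protocol does not define.

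**Working it through.** There is no plan figure to reproduce here. The check compares the rules with each other and then dates the windows.

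**Step 1: which causal link each rule requires**

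| Appendix 2 rule | Link required | Time limit |
|---|---|---|
| SAE definition (section 2) | trial drug or trial procedure | none stated |
| Automatic death reporting (section 2) | none | 30 days after last *study agent* dose |
| Later deaths (section 2) | *trial agent* | none |
| SUSAR definition (section 3) | trial drugs | none stated |
| AE collection (section 4) | none | 30 days after last *IMP* dose |
| SAE collection (section 5) | as in section 2 | starts at consent, no end stated |
| SUSAR reporting (section 6) | treatment or procedures | 30 days after the last treatment |

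An unexpected serious event attributed to the stent or its implantation is not a SUSAR under section 3. It is one under section 6 if stenting counts as trial treatment or procedure. The pointer in section 6 does not settle this. If it imports the whole of section 3, section 6 contradicts itself; if it imports only the meaning of *unexpected*, the two scopes still differ.

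**Step 2: when the 30-day windows close**

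Assumptions: the study agent, the IMP and the last treatment all mean prasugrel, and the full planned course is taken.

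Closing month = planned months of prasugrel + 30/30.4375.

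- DES, or BMS in ACS: 12 + 0.99 = 12.99, about month 13.
- Elective BMS: 1 + 0.99 = 1.99, about month 2.

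Share of follow-up covered = closing month / length of follow-up.

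| | 24 months | 60 months |
|---|---|---|
| DES, or BMS in ACS | 12.99/24 = 54% | 12.99/60 = 22% |
| Elective BMS | 1.99/24 = 8% | 1.99/60 = 3% |

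Among elective patients the DES window is 12.99/1.99, or about 6.5 times, as long as the BMS window. AE counts and automatically reported deaths are therefore not comparable between arms in that group.

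If aspirin is a study agent, the windows stay open for as long as it is taken. The text allows either reading.

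**Step 3: illustration only**

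The Background cites, for DES patients in a registry, "a rate of late angiographically documented stent thrombosis of 0,6% per year during the first 3 years of follow-up". Assume that rate for both trial DES, with 2 x 800 = 1600 patients and no dropout.

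- Months 13 to 24: 1600 x 0.006 x 11/12 = 8.8, about 9 thromboses.
- Months 13 to 36: 1600 x 0.006 x 23/12 = 18.4, about 18.
- At half the rate: 1600 x 0.003 x 11/12 = 4.4 and 1600 x 0.003 x 23/12 = 9.2.

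These are thromboses, not deaths, and not a count of missed SUSARs.

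**The case against.** The strongest defence is that safety capture is wider than the 30-day sentences suggest, and most of that defence stands.

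- **A reader might infer that all the serious-event rules are tied to the drug and stop at 30 days.** They are not and do not. The SAE definition includes trial procedures, SAE collection has no stated end, and section 10 of the protocol records SAEs during follow-up. The two death sentences add to the general fatal criterion; they do not replace it. A late stent death may also qualify through the catch-all for events that the investigator thinks need reporting. What remains is that nothing says whether the stent or its implantation is a trial procedure.
- **A reader might see a contradiction between the unlimited reporting in section 5 and the 30-day limit in section 6.** The recipients differ: the marketing authorisation holder in one, ethics committees and authorities in the other. Different limits can coexist. Section 6 also defers to local law and sets a minimum that does not bar later reports.
- **A reader might conclude that SAE death counts fail as the measure of stent safety.** The plan never uses them so. Stent safety is judged on cardiac death and MI, total death and ARC-defined stent thrombosis. End-points are adjudicated by a committee blinded to stent type, and the case report form records all deaths, hospitalisations and coronary interventions.
- **A reader might take the 9 and 18 events as the size of the reporting gap.** The rate comes from a registry of sirolimus- and paclitaxel-eluting stents, neither of which is a trial stent. A SUSAR must be unexpected, and the protocol treats stent thrombosis as a recognised risk.

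It can also be said that the appendix is about drugs and that section 11 calls none of the devices investigational. That would support a drug-only scope applied consistently, but section 6 of the appendix does not apply one. Nor does endpoint adjudication by itself notify an ethics committee or authority.

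**Conclusion.** The point holds as an inconsistency in expedited and automatic death reporting. The difference in scope between sections 3 and 6 of Appendix 2 is on the face of the text and needs no assumption. The timing gap rests on reading the agent, the IMP and the last treatment as prasugrel. On that reading, AE collection, required SUSAR reporting and automatic death reporting stop about 11 months before the 24-month endpoint after DES or after BMS in ACS, and about 22 months before it after elective BMS. On the aspirin reading the gap shrinks or disappears, and that the two readings lie so far apart is itself a defect.

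Outcome analysis is not impaired. Late stent-related events are still captured as adjudicated end-points, and as SAEs if the stent counts as a trial procedure. The documents give no basis for saying how many events would go unreported. The change is worth making because it bears on patient safety and costs little.

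**What to change.** Reword Appendix 2 as follows.

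1. Use one causality scope in sections 2, 3 and 6: trial drug, trial stent or its implantation, or trial procedure.
2. Define *study agent*, *trial agent*, *IMP* and *last treatment*, and say whether aspirin is included.
3. State one end of SAE, death and SUSAR reporting that is the same in all arms and does not depend on the drug course. If AE counts are to be compared between arms, put AE collection on the same footing.
4. In section 6, have unexpected serious events suspected to be related to drug, stent or procedure reported whenever the investigator learns of them.

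Making every death to month 60 an SAE is a policy choice for the sponsor and is not needed to remove the inconsistency.

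The cost is protocol wording plus some further SAE forms and causality assessments. Deaths, hospitalisations and coronary interventions are already recorded, so no new outcome data are needed.
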